**Fig. 1 Fig1:**
[figure not shown]
Standard Protocol Items: Recommendation for Interventional Trials (SPIRIT) schedule of enrollment, interventions and assessments

The stepped-wedge, cluster-randomized trial is a form of cross-over design with unidirectional cross-over (from control to intervention phase) at different time points for each cluster (Fig. 2). Each cluster will contain one center. Randomization will determine the order in which each center will undergo the transition [15, 16]. In the first timeframe, all centers will deliver current practice (i.e. control). In the second timeframe, the center in the first cluster will start with algorithm-based best practice (i.e. intervention), while all other centers will still deliver current practice. In the third timeframe, the second cluster will implement the algorithm. Following this approach, we proceed until all centers have stepped over to the algorithm. In the last timeframe, all centers will deliver treatment according to the algorithm. Each cluster will contain one center; therefore, the number of sequences is equal to the number of participating centers and this will be 17. To ensure adequate implementation of the algorithm, a wash-in period was designed in which clinicians in the center will be intensively trained by the research team on the algorithm. To avoid contamination of centers still in the current-practice phase, local clinicians will only have access to the algorithm after cross-over to care according to the algorithm.

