### Outcomes

All outcomes are assessed up to 90 days after the index pancreatic resection or, if admission exceeds 90 days, up to hospital discharge. All relevant definitions are provided in Table 1. The primary endpoint is a composite of the following three major complications occurring after study intervention:
New-onset postoperative bleeding requiring invasive interventionNew-onset organ failure (i.e. pulmonary, circulatory or renal)Death

**Table 1 Tab1:** Relevant definitions

New onset	Not present any time in 24 h before study intervention; accounts for all outcomes
Mortality	Rate of death occurring within 90 days after index pancreatic resection or, if index admission exceeds 90 days, during admission
Organ failure [12]	
Pulmonary	PaO2 < 60 mmHg, despite FiO2 of 0.3, or need for mechanical ventilation
Circulatory	Systolic blood pressure < 90 mmHg, despite adequate fluid resuscitation, or need for inotropic support
Renal	Creatinine level > 177 μmol/liter after rehydration or need for hemofiltration or hemodialysis
Post-pancreatectomy hemorrhage (PPH)	Adapted from Wente et al [18]
Grade A	Occurring < 24 h after pancreatectomy (*early*) with no therapeutic consequences
Grade B	Both early (< 24 h) and late (> 24 h) requiring therapy (including fluid or blood transfusion and transfer to high-care unit), with non-life-threatening clinical condition. Includes early PPH requiring relaparotomy
Grade C	Occurring > 24 h after pancreatectomy (*late*) with severely impaired, life-threatening clinical condition requiring intervention
Comprehensive Complication Index (CCI)	This summarizes all postoperative complications, other than pre-existing complications, in a score from 0 (no complications) to 100 (death). The CCI can be readily computed on the basis of tabulated complications according to the Clavien-Dindo classification [19, 20]
Postoperative pancreatic fistula	Amylase in drain fluid on or after postoperative day 3 of at least three times the upper level of normal serum amylase [21]
Biochemical leak	Requiring no change in postoperative management, hospital stay not prolonged
Grade B	Persistent drainage > 3 weeks, change in postoperative management (i.e. catheter drainage, or angiographic procedure for bleeding, signs of infection without organ failure, no relaparotomy), all related to pancreatic fistula
Grade C	Grade B with reoperation, organ failure or death related to pancreatic fistula

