Postoperative bile leakage	Bilirubin in drain fluid on or after postoperative day 3 of at least three times the upper level of normal serum bilirubin (adapted from Koch [22])
Delayed gastric emptying	Adapted from Wente et al [23]
Grade A	Nasogastric tube postoperative day 4–7 or need for replacement of tube after postoperative day 3; oral intake between day 7 and 14
Grade B	Nasogastric tube postoperative day 8–14 or need for replacement of tube after postoperative day 7; oral intake between day 14 and 21
Grade C	Nasogastric tube after postoperative day 14 or need for replacement of tube after postoperative day 14; oral intake after day 14
Gastroenterostomy leakage	As seen on abdominal imaging or during relaparotomy or secretion of fecal material from percutaneous drain or through surgical wound
Acute pancreatitis	Combination of abdominal pain, threefold increased amylase and lipase levels or as seen on radiologic imaging [24]
New-onset diabetes mellitus	Need for insulin or oral diabetes drugs within 3 months after discharge, not present before pancreatoduodenectomy
Exocrine pancreatic insufficiency	Need for oral pancreatic-enzyme supplementation within 3 months after discharge, not present before pancreatoduodenectomy
Body mass index	Weight in kilograms divided by the square of the height in meters
ASA	American Society of Anesthesiologists classification
I	Healthy patient without systemic disease
II	Patient with mild systemic disease
III	Patient with severe systemic disease, limiting activity but not life-threatening

*PaO2* arterial partial pressure of oxygen, *FiO2* fraction of inspired oxygen

The rationale for this primary endpoint is that the proposed algorithm for early detection and step-up management of pancreatic fistula can possibly prevent clinical deterioration. The most clinically severe complications associated with pancreatic fistula are combined in this endpoint [8]. Members of an adjudication committee will individually asses the primary endpoint while blinded to the assigned treatment arm; disagreements will be resolved by consensus discussions, with allocation concealment.

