Secondary endpoints include individual components of the composite endpoint and an adapted version of the primary endpoint in which only complications are included that are deemed by the blinded adjudication committee to be directly related to a pancreatic fistula. Other secondary endpoints are: the Comprehensive Complication Index (CCI) [25] based on complications grade 3 or higher according to the Clavien-Dindo classification [19], postoperative pancreatic fistula [21], gastroenterostomy leakage, postoperative bile leakage [22], delayed gastric emptying [23], chyle leakage [26], new-onset acute pancreatitis [24], number and timing of abdominal CT scans, number, timing and type of invasive (re-)interventions, admission to the Intensive Care Unit (ICU), length of ICU stay, length of hospital stay, readmission rate, number of patients receiving adjuvant chemotherapy at 90 day follow up, duration of postoperative pancreatic fistula (time to removal of the last abdominal drain or completion of pancreatectomy), success of implementation (i.e. based on number and timing of abdominal CT scans and proportion of patients’ days in which the algorithm was not followed). Daily data on the incidence and duration of SIRS, sepsis and organ failure (according to the definitions in Table 1 and according to Sequential Organ Failure Assessment (SOFA) and the Multiple Organ Dysfunction Score (MODS)) are also collected [27–29]. In addition, we aim to evaluate the impact on quality of life, total direct and indirect costs and budget impact (see “Economic evaluation”).

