### Subgroup and sensitivity analyses

Analyses will be performed both on the group of patients undergoing pancreatoduodenectomy and on the entire group of all patients undergoing pancreatic resection. Additional subgroup analyses will be performed based on adherence to the study protocol (i.e. proportion of patients’ days in which the algorithm is followed), hospital volume (> 45 vs. ≤ 45 pancreatic resections a year), pathologic nature of disease (malignant disease), in patients with postoperative pancreatic fistula and in patients with a high risk of pancreatic fistula [34].

A sensitivity analysis will be performed to evaluate the impact on outcomes related to postoperative pancreatic fistula. To this aim, the adjudication will be asked if an outcome was related to postoperative pancreatic fistula and if this outcome could have been prevented by adherence to the algorithm. Two separate analyses will be performed on the Comprehensive Complication Index: one analysis including all complications and one adjusted analysis, in which interventions imposed by the algorithm (e.g. minimal invasive catheter drainage and use of antibiotic management for abdominal sepsis) will not be included in the calculation. A sensitivity analysis will be performed to evaluate the success of implementation. Centers will be divided into equally sized clusters based on the percentage of additional abdominal CT scans per patient after implementation, as compared with before implementation. Separate analysis will be performed for each group.

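### Three secondary-endpoint scoring rules need correcting: read literally, the adjusted complication index drops procedures after cross-over only; its grade threshold varies; and delayed gastric emptying grades overlap

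*Protocol article*

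**What the plan says.** **Adjusted CCI.** The section on subgroup and sensitivity analyses plans two analyses of the index: "one analysis including all complications and one adjusted analysis". In the second, "interventions imposed by the algorithm (e.g. minimal invasive catheter drainage and use of antibiotic management for abdominal sepsis) will not be included". It does not say how the same procedures are handled in patients operated on before cross-over. The trial design section states that "local clinicians will only have access to the algorithm after cross-over to care according to the algorithm". The Intervention section adds that the algorithm structures procedures which centers already employ, so drainage and antibiotics occur in both phases.

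**Scope of the CCI.** The list of secondary endpoints in the Outcomes section has the index "based on complications grade 3 or higher according to the Clavien-Dindo classification". Table 1 defines it without a threshold: "This summarizes all postoperative complications, other than pre-existing complications, in a score from 0 (no complications) to 100 (death". The sensitivity section refers to all complications and does not mention grade 3.

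**Delayed gastric emptying.** Table 1 gives the oral-intake part of grade B as "oral intake between day 14 and 21". Grade C reads "Nasogastric tube after postoperative day 14 or need for replacement of tube after postoperative day 14; oral intake after day 14". Grade A covers oral intake from day 7 to day 14. Delayed gastric emptying is a listed secondary endpoint.

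**The concern.** A score that leaves out certain procedures compares the phases fairly only if it leaves them out in both. The exclusion here is worded by what prompted the procedure, and that prompt exists in one phase only. An analyst who follows the words would lower the index after cross-over even if the algorithm changed nothing.

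The other two items are definitional. With two scopes for one index, the choice of which is the secondary endpoint stays open until the data are seen. With overlapping grades, a patient can be coded into either of two adjacent grades, and the article states no tie-break.

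**Working it through.** **1. Adjusted CCI.** The plan gives no figure to reproduce. Let p0 and p1 be the shares of patients with a listed procedure before and after cross-over, k the mean index points that the procedure contributes per such patient (taken as equal in both phases), and D the difference in mean index, after minus before, from everything else.

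- All complications counted: D + k(p1 - p0)
- Listed procedures removed in both phases: D
- Listed procedures removed after cross-over only: D - k·p0

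Against symmetric removal, the one-sided rule adds -k·p0. This always favors the algorithm, because a lower index is better. If the procedures are equally common in both phases (p0 = p1 = p) and there is no true effect, the one-sided rule gives -k·p and the other two give 0.

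The document supplies neither k nor p0. For illustration only, the Background gives 13% for clinically relevant fistula in a systematic review and 73% for primary catheter drainage in a severe-fistula cohort. Their product is 0.13 × 0.73 = 0.095, although the two figures come from different populations. The 20% share and the values of k are assumptions.

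| Share p | k = 5 | k = 10 | k = 20 |
|---|---|---|---|
| 9.5% (13% × 73%) | -0.47 | -0.95 | -1.90 |
| 13% | -0.65 | -1.30 | -2.60 |
| 20% (assumed) | -1.00 | -2.00 | -4.00 |

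The table shows direction and rough order only.

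**2. Scope of the CCI.** Side by side: the endpoint list counts grade 3 or higher; Table 1 counts all complications; the sensitivity section plans one analysis of all complications and one reduced analysis. Table 1 can be taken as a description of the instrument. The endpoint list and the sensitivity section still disagree unless all complications is meant as all that reach grade 3, and the text does not say so.

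**3. Delayed gastric emptying.** Checking each whole day of oral intake against Table 1:

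| Day of oral intake | Grades met |
|---|---|
| 7 to 13 | A |
| 14 | A and B |
| 15 to 21 | B and C |
| 22 and later | C |

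Seven of the eight days in the grade B window (14 to 21) also meet grade C. If the worst grade is taken, the grade B oral-intake criterion keeps day 14 alone. The bands for a tube in place (days 4 to 7, 8 to 14, after 14) do not overlap. The tube-replacement criteria (after day 3, 7 and 14) are nested, and a worst-grade rule would settle them.

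**The case against.** On the CCI, the exclusion names procedure types as examples, and those types are used in both phases. The sentence can therefore be read as dropping them throughout. The reduced index is one of two planned analyses, and the all-complications version would expose an artefact as a gap between the two. Coding detail for a sensitivity score might also sit in a fuller document. Most of this stands: the rule is ambiguous rather than self-contradictory, and its reach is limited. It does not remove the point, because the criterion as printed is what the algorithm imposed, and that wording selects one phase.

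On scope, planning two versions is deliberate and is no contradiction in itself. What remains is the missing link between the grade 3 threshold and the sensitivity section.

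On delayed gastric emptying, a worst-grade convention would resolve the overlap, and no stated analysis uses the split between B and C. Also true, but the convention is not stated, and it would leave the grade B oral-intake entry almost empty.

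A reader might infer more than the documents support:

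- That the dropped procedures exist only after cross-over. The article says the opposite.
- That bias is certain by construction. It follows from the literal reading only.
- That the reduced index is meant as the fairer of the two. Nothing ranks it above the other.
- That grade C should begin after day 21. The pattern of A and B suggests it, but the document cannot show which entry is in error, and the cited definition is not at hand.

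**Conclusion.** The point holds as a correction to three secondary-endpoint definitions. The adjusted CCI rule, read literally, biases that one analysis toward the algorithm, by an amount the document does not allow to be calculated; the point values above rest on assumed inputs. The CCI's scope is stated inconsistently. The delayed gastric emptying table assigns two grades to oral intake on days 15 to 21 (B and C) and on day 14 (A and B), which affects the grade and not whether the condition is present. The primary endpoint, the sample size and the main inference are untouched.

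**What to change.** 1. In the adjusted CCI, omit the same listed procedure types (percutaneous drainage, antibiotics for abdominal sepsis) in both phases, whatever prompted them. Report the all-complications version beside it. The small downside is that even symmetric removal hides extra drainage, and the Discussion expects drainage to increase; the companion analysis keeps that visible.
2. Name one CCI version as the secondary endpoint, label the other as sensitivity, and use the same wording in the Outcomes section, Table 1 and the sensitivity section.
3. Reconcile the grade A, B and C oral-intake entries with each other and with the cited definition so that the grades are exclusive, without presuming which entry is wrong. State how a patient who meets criteria of more than one grade is classified.

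The cost is a few sentences and a coding check of records already entered. The article reports that recruitment was still under way at submission, so the changes could be fixed before analysis.

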In general, in-hospital mortality after pancreatoduodenectomy varies widely among Dutch centers (interquartile range 0–8%). This variability appears to be explained by differences in failure-to-rescue rates between centers (i.e. mortality in patients with major postoperative complications) [11]. A recent multicenter propensity-score-matched study by the Dutch Pancreatic Cancer Group identified doubling of mortality after primary relaparotomy, as compared with primary minimally invasive catheter drainage for postoperative pancreatic fistula (36% vs. 14%, *P* = 0.007; risk ratio 0.39; 95% confidence interval 0.20–0.75) [9]. Relaparotomy causes a major inflammatory response syndrome in patients who are already ill, which might induce or aggravate multiple organ failure and possibly death [12]. As an alternative to relaparotomy, minimally invasive percutaneous catheter drainage has been shown to be very effective in the majority of patients [9]. In daily practice, however, both treatment strategies are still frequently performed (primary catheter drainage 73%, primary relaparotomy 27%) with no change towards a more minimally invasive management strategy [9]. This might be related to the lack of (international) guidelines on postoperative patient monitoring and management of complications.

This trial is designed to investigate whether implementation of an algorithm for postoperative care focusing on early detection and minimally invasive step-up management of postoperative pancreatic fistula results in a lower rate of major complications and death after pancreatic resection, as compared with current practice. This trial will also evaluate the superiority of the algorithm in other clinical outcomes, the number of patients receiving chemotherapy, quality of life, healthcare resource utilization and costs.

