A schematic overview of the multilevel algorithm is provided in Fig. 3. It is based on daily standardized evaluation of all patients undergoing pancreatic resection from postoperative day 3 to discharge up to a maximum of 14 days. The algorithm will provide daily advice on three decision levels: indication for abdominal computed tomography (CT) scan (Fig. 4); indication for (invasive) intervention (i.e. minimally invasive percutaneous drainage and/or antibiotic treatment) based on evaluation of the abdominal CT scan (Fig. 5) and indication for removal of abdominal drain(s) (Fig. 6). The algorithm includes clinical data from physical examination and biochemical tests (i.e. systemic inflammatory response syndrome (SIRS), C-Reactive protein (CRP), white blood cell count (WBC), drain production including amylase content and a daily consult from a pancreatic surgeon). At predefined, evidence-based cutoff points (Fig. 4), an abdominal contrast-enhanced CT scan and possibly subsequent minimally invasive intervention should be performed or antibiotic treatment should be started (Fig. 5). Each CT scan will be evaluated according to predefined criteria (Fig. 5) to assess whether there is suspicion of a pancreatic fistula and whether there is an indication for minimally invasive percutaneous catheter drainage. In the case of no clinical improvement within 48 h after the last CT scan, a further CT scan should be performed to assess the indication for and possibility of (additional invasive) intervention. The indication to remove abdominal drains will be evaluated daily starting on postoperative day 3, for as long as there are abdominal drains in place (Fig. 6). The interpretation of the algorithm, the rationale behind the different proposed cutoff points and the proposed management of bleeding or hepaticojejunostomy leakage is provided in Additional file 1: Appendix 2. Since we propose an intervention of structured use of diagnostic and invasive interventions that are already used in daily practice, no additional harms to patients are introduced in this study.

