The management of pancreatic fistula after pancreatic resection is shifting from relaparotomy to a more conservative approach using minimally invasive catheter drainage. Pancreatic fistula after pancreatoduodenectomy leads to an intra-abdominal fluid collection filled with activated pancreatic juices. When drained adequately, even a severe pancreatic fistula could resolve with primary catheter drainage alone [9]. In addition, percutaneous drainage is a minimally invasive procedure, which will provoke less surgical trauma (i.e. tissue injury and systemic inflammatory response) compared with relaparotomy. Even moderately small surgical trauma that induces a proinflammatory cytokine response can lead to organ failure in severely ill patients [12]. There is, however, still a significant number of patients in whom pancreatic fistula is managed primarily through laparotomy. Clinical outcomes might be improved using a step-up approach with primary catheter drainage and relaparotomy as a salvage option in patients who continue to deteriorate without further options for minimally invasive drainage.

This trial has several limitations. Even though a stepped-wedge, cluster-randomized trial is less efficient as compared with a conventional individual randomized trial, this is the only appropriate design to evaluate our research question, which is based on education in “best practice care” involving early detection and management of pancreatic fistula. With a design based on individual-level randomization, contamination of the control group would have been very likely due to the learning effect of applying the algorithm in the intervention group. The more efficient, cluster-randomized, cross-over design, in which half of the clusters crosses over from control to intervention and the other from intervention to control, is also prohibited due to the learning effect. Moreover, a stepped-wedge design was also chosen for logistical reasons, i.e. the aim is to implement the algorithm in all Dutch pancreatic centers and it is not feasible to roll out an education-based intervention with very active participation of the study team in more than one center simultaneously. Additionally, after calculating the statistical efficiency, the power achieved from a stepped-wedge, cluster-randomized trial was considerably higher than that of a parallel cluster-randomized trial, which is due to relatively high intra-cluster correlation.

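### The adjusted Comprehensive Complication Index leaves out algorithm-imposed drainage but does not say that the rule also holds before cross-over, so identical care can score differently by phase

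*Protocol article*

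**What the plan says.** The Comprehensive Complication Index is a secondary endpoint. Under Subgroup and sensitivity analyses the protocol article states: "Two separate analyses will be performed on the Comprehensive Complication Index: one analysis including all complications and one adjusted analysis". In the adjusted one, "interventions imposed by the algorithm (e.g. minimal invasive catheter drainage and use of antibiotic management for abdominal sepsis) will not be included".

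Three other places bear on how that rule works:

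- **Intervention** describes the treatment level of the algorithm as "indication for (invasive) intervention (i.e. minimally invasive percutaneous drainage and/or antibiotic treatment) based on evaluation of the abdominal CT scan". Relaparotomy is not in that list, and the Discussion describes a "step-up approach with primary catheter drainage and relaparotomy as a salvage option".
- **Trial design** gives local clinicians access to the algorithm only after their center has crossed over.
- **Background** gives the mix of first treatments in current practice as "primary catheter drainage 73%, primary relaparotomy 27" (both per cent).

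On what the index counts, Outcomes says it is "based on complications grade 3 or higher according to the Clavien-Dindo classification", while Table 1 describes the index as covering all postoperative complications that were not pre-existing.

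**The concern.** An outcome compared between two phases has to be scored by the same rule in both. Here the exclusion depends on whether the algorithm imposed the intervention, and that can be true only after cross-over. The article does not say that the same drains and antibiotics are also left out in the current-practice phase.

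A second problem remains if the rule is applied to both phases. The algorithm is meant to put drainage in the place of primary relaparotomy. The adjusted index makes the replacing treatment free and, as far as the text shows, goes on scoring the treatment that is replaced.

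At stake is the reading of one secondary endpoint. A reader who sees two index results, one clearly lower under the algorithm, may take the lower one as fewer complications when part of the difference is a scoring rule.

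**Working it through.** The protocol article gives no planned figure for the index, so there is none to reproduce. One check on the input mix is possible. Sample size calculation gives the primary endpoint as 34% after primary drainage and 73% after primary relaparotomy, and 0.73 × 34% + 0.27 × 73% = 24.8% + 19.7% = 44.5%. This agrees with the 44% in Table 2, so the 73/27 mix belongs to the 2005–2013 cohort with severe fistula.

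**Inputs**

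- Relaparotomy share before cross-over: 0.27; drainage share: 0.73 (Background).
- Points for one drain, d, and one relaparotomy, r: not in the document. Assumed d = 26.2 and r = 33.7; also tried 20/30, 30/40 and 30/30 (d/r).
- Simplification: one scored first treatment per treated fistula, with contributions added.

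**Formulas, per treated fistula, with relaparotomy share x**

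- Full index: x·r + (1 − x)·d
- Adjusted, drains left out in both phases: x·r in each phase
- Adjusted, drains left out only after cross-over: 0.27·r + 0.73·d before, x·r after

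**Results at d = 26.2, r = 33.7**

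Before cross-over the full index is 0.27 × 33.7 + 0.73 × 26.2 = 9.10 + 19.13 = 28.2.

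| Relaparotomy share | Full index | Adjusted, both phases | Adjusted, after cross-over only |
|---|---|---|---|
| 27% to 27% (no change) | 28.2 to 28.2 | 9.10 to 9.10 | 28.2 to 9.10 |
| 27% to 13.5% (illustration) | 28.2 to 27.2 (−3.6%) | 9.10 to 4.55 (−50%) | 28.2 to 4.55 |

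**Reading the first row.** With no change in care, the rule applied to both phases gives no fall. Applied only after cross-over, it gives a fall of 0.73 × 26.2 = 19.1 points per treated fistula.

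**Reading the second row.** Each relaparotomy replaced by a drain moves the full index by r − d and the adjusted index by r. The ratio is r/(r − d):

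- 33.7/7.5 = 4.5
- 30/10 = 3.0 for r = 30, d = 20
- 40/10 = 4.0 for r = 40, d = 30
- if r = d, the full index does not move and the adjusted one still falls by half

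**Added drainage.** The Discussion expects more drainage procedures across the study population. Ten extra drained patients per 100 add 0.10 × 26.2 = 2.6 points to the full mean and nothing to the adjusted mean in the algorithm phase.

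**Rough scale per patient, literal rule, no change in care.** Take the 13% rate of clinically relevant fistula in Background and suppose that every such fistula has one scored first treatment and every drain counts as imposed. Then 0.13 × 0.73 × 26.2 = 2.5 points, or 1.9 to 2.8 for d from 20 to 30. This combines a rate from an international review with a mix from a severe-fistula cohort. It also overstates the share treated by an intervention, because grade B in Table 1 includes fistulas defined by prolonged drainage or signs of infection. It is an illustration, not an estimate.

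**The case against.** The strongest case on the other side has five parts.

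- **The adjusted version has a proper purpose.** An index graded by treatment counts every algorithm-advised drain as a complication, so the full index leans against the algorithm. Wanting a version without that penalty is reasonable. This stands. It does not justify a rule that differs by phase, or one that frees only the replacing treatment.
- **The plan already brackets the result.** The all-complications index is planned alongside, and the number, timing and type of re-interventions are secondary endpoints. The primary endpoint is untouched. This stands, and it limits the consequence.
- **An avoided relaparotomy may be a real gain.** Background reports mortality of 36% after primary relaparotomy against 14% after primary drainage. A reader might infer that the adjusted index falls after implementation by construction, with no patient better off. The document does not support that in general: with drains left out in both phases and relaparotomy steady at 27%, the index does not move. A shift away from relaparotomy would also lower the full index if r exceeds d. What remains is an exaggerated size.
- **Relaparotomy is kept only by inference.** The excluded interventions are introduced as examples, and details of the algorithm are in an additional file that is not shown. This stands as a caution. The list under Intervention and the salvage role in the Discussion make the inference the natural one.
- **Antibiotics may not matter.** If only grade 3 and above is scored, leaving them out may change nothing. The document does not settle this.

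The scoring detail could be fixed in an analysis plan that is not shown. The point here is the rule the article does state, which ties exclusion to something that exists in one phase only.

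**Conclusion.** The concern holds in limited form. Read literally, the exclusion defines the outcome differently by phase and lowers the algorithm-phase score even if care is unchanged. Read as applying to both phases, it does not lower the score by definition. It does exaggerate any shift from relaparotomy to drainage, about 3 to 4.5 times the fall in the full index at the weights tried, and it gives added drainage no cost.

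The sizes rest on assumed index weights, on one scored treatment per fistula and on a mix from a severe-fistula cohort. Within that simple model the directions do not depend on the exact weights. A reader might go on to infer that the artefact alone would reach statistical significance. The document gives neither the weights nor a standard deviation for the index, so no such claim can be made.

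The effect is confined to a supportive analysis of one secondary endpoint.

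**What to change.** Changes to the analysis wording:

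1. Define the exclusion by event type, not by whether the algorithm imposed the intervention, and state that the same types are left out before and after cross-over.
2. Name the all-complications index as the main index analysis and label the adjusted one supportive.
3. State whether relaparotomy is scored in the adjusted index. Show drainage and relaparotomy rates by phase beside it, or add a version that leaves out all fistula interventions, relaparotomy included, in both phases.
4. Reconcile Outcomes, Table 1 and Subgroup and sensitivity analyses on whether the index counts all complications or only grade 3 and above. If the all-complications analysis only means that nothing is excluded within grade 3 and above, say so.

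No extra data are needed beyond the complications and re-interventions already planned. The downside is that the adjusted result may look less favourable to the algorithm, and a version without relaparotomy gives no credit for relaparotomies avoided. The full index and the re-intervention endpoint still show that. Replacing the adjusted index by one that scores only bleeding, organ failure, intensive care admission and death is not needed, since it would largely repeat the primary endpoint.
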